### MRI acquisition

Participants were scanned using 3T Siemens Magnetom Prisma scanner equipped with a 32-channel head coil. T1-weighted images were acquired using a MPRAGE protocol (TE = 2.45 ms; TR = 2200 ms; FOV = 263 × 350 × 350 mm; voxel size = 1 mm isotropic). Resting-state fMRI scans were acquired using a multiband EPI sequence (TR = 719 ms; TE = 30 ms; 60 axial slices; FOV = 220 × 220; voxel size = 2.5 mm isotropic). During the resting-state fMRI scan, subjects were instructed to remain awake and lie still with their eyes open while looking at a fixation cross. Additionally, gradient echo field maps (TR = 615 ms; TE1 = 4.92 ms; TE2 = 7.38 ms) were acquired for correcting the rsfMRI distortions. Diffusion-weighted images were acquired using a multi-shell multiband protocol consisting of 13 b0 images, 5 directions at b = 500 s/mm^2^, 48 directions at b = 1000 s/mm^2^ and 60 directions at b = 1000 s/mm^2^ (TE = 71 ms; TR = 3400 ms; phase encoding = *A*>>*P*; FOV = 232 × 232; 127 axial slices; voxel size = 1 × 1 × 2 mm). An additional b0 vol were acquired in the reversed encoding direction (*P*>>*A*) for the purpose of distortion correction. T2-weighted FLAIR sequences were acquired using a SPACE sequence (TR = 7000 ms; TE = 393 ms; TI = 2100 ms; 192 axial slices; FOV = 256 × 256 mm; voxel size = 1 mm isotropic).

### Image preprocessing

The T1 structural images will be preprocessed with FreeSurfer 7.2.0 using the default recon-all options. Briefly, this processing included the removal of non-brain tissue using a hybrid watershed/surface deformation procedure [36], automated Talairach transformation, segmentation of the subcortical white matter and deep gray matter volumetric structures (including hippocampus, amygdala, caudate, putamen, ventricles) [37,38], intensity normalization [39], tessellation of the gray matter white matter boundary, automated topology correction [36,40], and surface deformation [41,42]. Once the cortical models are completed, they will be registered to a spherical atlas which is based on individual cortical folding patterns to match cortical geometry across subjects [43], and the cerebral cortex will be parcellated into units with respect to gyral and sulcal structure. This method used both intensity and continuity information from the entire three-dimensional MR volume in segmentation and deformation procedures to produce representations of cortical thickness, calculated as the closest distance from the gray/white boundary to the gray/CSF boundary at each vertex on the tessellated surface [42]. The preprocessed cortical thickness images will subsequently resampled onto the fsaverage6 space and smoothed using a 5 mm kernel.

Resting-state fMRI scans will be preprocessed using fMRIPrep 22.0.2 [44]. Functional data will be slice time corrected using 3dTshift from AFNI [45] and motion-corrected using MCFLIRT [46]. This process will be followed by co-registration to the corresponding T1w using boundary-based registration [47] with 9 degrees of freedom, using bbregister from freesurfer. Motion correcting transformations, BOLD-to-T1w transformation, and T1w-to-template (MNI) warp will be concatenated and applied in a single step using antsApplyTransforms employing Lanczos interpolation. Subsequently, these preprocessed volumes are denoised by regressing out 6 motion parameters, the average signal of white matter and cerebrospinal fluid masks, global signal, and their derivatives, as well as cosines covering slow time drift frequency band using the ‘nilearn’ library in Python. Then, these volumes will be subjected to a 0.1 Hz low-pass filter. Scrubbing will be carried out using the Power approach [48] to further remove the effects of excessive head motion. These volumes will then be smoothed using a 5 mm FWHM kernel and subjected to a 0.1 Hz low-pass filter. Finally, the brainnetome atlas [49] will be used to parcellate the whole brain into 246 anatomical regions corresponding to the nodes of the network. Participants with excessive head motion (root mean squared displacement >0.25) will excluded from the analyses.

The preprocessing of the diffusion images, tractography, and construction of the structural connectome will be carried out using MRtrix3 (version 3.0.3) [50]. Briefly, MP-PCA denoising [51] and removal of Gibbs ringing artifacts [52] will be carried out on the raw images. Subsequently, they are corrected for motion, eddy currents and susceptibility-induced distortion using the inhomogeneity field maps obtained previously. Following this, bias field correction [53] will be carried out. Next, the gray matter (GM), white matter (WM), and cerebrospinal fluid (CSF) response functions will be obtained using the Dhollander algorithm [54] which are in turn used for estimating fiber orientation distributions (FOD) in the WM, GM and CSF tissues from diffusion data using spherical deconvolution. Then, anatomically-constrained tractography [55] will be carried out using the WM FOD. This involved the prior preparation of a GM mask from the Freesurfer segmentations and then using this mask to seed streamlines. The AAL-90 atlas [56] will be used to parcellate the whole brain into 90 regions for the construction of the structural connectome. The edges in the connectivity matrix will be operationalized as the number of streamlines connecting between each pair of regions.

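### As printed, the resting-state pipeline low-pass filters before scrubbing and again afterwards, so brief motion artefact can spread into frames that scrubbing keeps

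*Protocol article*

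**What the plan says.** The Image preprocessing section gives the resting-state steps in sequence. After slice-timing and motion correction, registration and resampling, the volumes are "denoised by regressing out 6 motion parameters, the average signal of white matter and cerebrospinal fluid masks, global signal, and their derivatives", together with cosine drift terms. The next two steps read: "Then, these volumes will be subjected to a 0.1 Hz low-pass filter. Scrubbing will be carried out using the Power approach". After that: "These volumes will then be smoothed using a 5 mm FWHM kernel and subjected to a 0.1 Hz low-pass filter". Parcellation into 246 regions follows.

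The same 0.1 Hz filter therefore stands on both sides of scrubbing. The article does not say whether flagged frames are deleted or interpolated, and gives no reason for filtering twice.

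There is one participant-level safeguard: "Participants with excessive head motion (root mean squared displacement >0.25) will excluded from the analyses".

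The MRI acquisition section gives the sampling interval: "TR = 719 ms; TE = 30 ms; 60 axial slices". The Data analysis section relates functional networks to behavioural and diagnostic variables with network-based statistics. Hypothesis 3(ii) concerns connectomes in relation to cognitive decline, depression and anxiety.

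**The concern.** Scrubbing removes frames spoiled by brief head movement. It works best while the damage is still confined to those frames. A temporal filter is a weighted average over neighbouring frames, so applying it first moves part of the artefact into frames that scrubbing will not flag.

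A second issue depends on something the article leaves open. If scrubbing deletes frames, the second filter treats frames on either side of a gap as consecutive.

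At stake are the functional-connectivity results under hypothesis 3(ii). Residual motion artefact alters edge estimates. If the amount of motion also varies with cognitive status or mood, that alteration can look like a brain-behaviour association.

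**Working it through.** The article states no figure that depends on this order, so there is none to reproduce. The check covers the mechanism and its possible size.

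**1. Spread of a one-frame spike**

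From the article: repetition time 0.719 s, cut-off 0.1 Hz. The Nyquist frequency is 1/(2 × 0.719) = 0.695 Hz, so the cut-off is 0.1/0.695 = 0.144 of Nyquist. The filter type is not given; I assume a zero-phase Butterworth and vary its order.

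With h(k) the filter's response k frames from the spike, the share of filtered energy outside a censoring window W is

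1 − Σ(k in W) h(k)² / Σ(all k) h(k)².

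| Butterworth order | Outside −1 to +2 frames |
|---|---|
| 1 | 19% |
| 2 | 32% |
| 3 | 38% |
| 4 | 41% |
| 5 | 42% |

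At order 5, 84% lies outside the spike frame itself and 3.8% outside ±5 frames. Over orders 1 to 5 the share outside ±5 frames is about 1 to 4%. The response stays above 10% of its peak for 11 to 21 frames, that is 11 × 0.719 = 7.9 s to 21 × 0.719 = 15.1 s.

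So the spread occurs for every filter order tried. How much survives scrubbing depends strongly on the width of the censoring window, which the article does not state.

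**2. Effect on correlations, without nuisance regression**

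Assumptions: two unrelated regions (true r = 0), 500 frames, shared spikes of 3 to 10 times the in-band signal SD (about 1), window −1 to +2, order 5. Mean correlation:

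| Spikes, scale | Printed order, frames deleted | First filter only | Censor and interpolate, then filter once | No motion |
|---|---|---|---|---|
| 10, 3 | 0.008 | 0.011 | 0.000 | −0.001 |
| 25, 5 | 0.054 | 0.077 | 0.006 | 0.005 |
| 50, 10 | 0.287 | 0.384 | 0.016 | 0.014 |

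Censoring first removes the bias. Striking out only the second filter does not, because the first filter does the spreading. These figures are not estimates for this study, since they leave out the regression that the article specifies.

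**3. Effect with global-signal regression**

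With the global signal and its derivative regressed before filtering, the mean shift in correlation is zero. Global-signal regression largely fixes the mean, so single edges have to be examined as well:

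- Over assumed spike rates of 1 to 10% and scale 3 to 5, the edge-specific bias is 0.007 to 0.066 root mean square in the printed order, against 0.005 or less when frames are censored first.
- In a separate setting (60 regions, 500 frames, 1 or 5% of frames hit, scale 3 or 5), the bias is 0.000 to 0.006 with independent regions and 0.002 to 0.083 when a shared neural signal is added.

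Harm to individual edges is therefore possible, and its size depends on the assumptions.

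**The case against.** **The order may be a drafting slip.** The filter appears twice in nearly the same words, and the scrubbing sentence has no sequence word. If the first mention is the stray one, the order is regression, scrubbing, smoothing, filter, and the spreading disappears. This stands as a possibility. It does not remove the need for a correction, because the text as printed says otherwise. If the second mention is the stray one, the spreading remains.

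**The gaps are inferred.** This stands. A reader might infer that the second filter certainly runs on a gapped series. The article only names a published scrubbing approach and does not say that frames are deleted.

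**Other steps deal with motion.** This stands in part. A reader might infer from section 2 of the check that connectivity is inflated across the board. With the stated global-signal regression there is no such mean shift, so that reading fails. Edge-level bias remains possible, and the article itself adds scrubbing to deal with motion left after regression. The exclusion of participants with high displacement acts on whole people, not on brief movements in those retained.

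**The harm is conditional.** This stands. Nothing in the article shows that motion differs by cognitive status or mood. The MRI visit also excludes people found to have dementia or reporting psychiatric or neurological conditions, which may narrow such differences.

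**Conclusion.** The point holds as a defect in the stated order of processing. As printed, the first 0.1 Hz filter spreads brief motion artefact into frames that scrubbing may keep: about 19 to 42% of the filtered energy for a −1 to +2 frame window, but only about 1 to 4% for ±5 frames. Given the stated global-signal regression, the consequence to expect is edge-specific bias, about 0.01 to 0.07 root mean square in the main simulation, and not a general rise in correlations.

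These sizes rest on an assumed filter type, censoring window, spike rate and spike amplitude. Few or small spikes, or independent regions, bring the bias close to zero.

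The article does not support a claim that the hypothesis 3(ii) results will be false. That needs motion to vary with cognitive status or mood, on which it is silent. The change is still worth making, because the better order removes nearly all of the bias at little cost.

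**What to change.** State the order once, and change it to:

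1. Flag frames from the unfiltered motion parameters.
2. Interpolate the flagged frames, or add spike regressors for them.
3. Run the nuisance regression and a single 0.1 Hz low-pass filter.
4. Drop the flagged frames, then smooth and parcellate.

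Delete the duplicate filter, and say how flagged frames are handled.

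The cost is a script change and computing time; no participants or scans are lost. The section describes these steps in the future tense, but the article also reports that analyses are under way. If the pipeline has already run in the printed order, up to 300 scans need reprocessing and their connectivity analyses repeating. If the first mention of the filter is a drafting repeat, it is enough to correct the text and confirm that flagged frames are interpolated before filtering.

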## Data analysis

All demographic variables would be presented as descriptive summaries, such as means, standard deviations, median, standard errors and percentages, depending on the parametric/ non-parametric nature of the data. Non-parametric measures were normalized before being subjected to analyses.

To examine hypothesis 1, chi-square analyses were performed to investigate any changes in frequency of groups, i.e., normal ageing, MCI and dementia, across the 3-year period. Cognitive scores of participants from the LFC study were compared with their respective scores in the CHI study using dependent-samples *t*-tests.

As for hypothesis 2, potential differences of cognitive functioning, psychosocial outcomes and speech characteristics between groups, i.e., normal ageing, MCI and dementia, were analysed using independent-sample *t*-tests and Analysis of Variance (ANOVA).

To investigate hypothesis 3, cross-sectional brain-behaviour associations were examined via whole-brain approaches, n across various MRI modalities such as cortical thickness, structural connectivity resting state functional connectivity. Network-based statistics were used to identify structural and functional brain networks corresponding to behavioural and diagnostic variables. As for cortical thickness, whole-brain vertex-wise associations with behaviour will be analysed using the ‘standard linear regression’ module in the ‘BrainStat’ Python library [57]. The random field theory (RFT) correction, which corrects the probability of ever reporting a false positive result, was applied with a cluster-defining threshold of *p*<0.05.

Relationships between cognitive decline and various psychosocial outcomes such as depression and anxiety symptoms, quality of life and social connectedness were analysed using multiple regressions and structural equation models. Speech characteristics such as speech rate and concreteness were obtained after audio recordings are transcribed. Speech rates of various nouns and verbs were calculated by dividing the total number of nouns and verbs by the total number of minutes. Concreteness scores were obtained based on the concreteness ratings of 40,000 English words assembled by Brysbaert et al. [58]. Associations between these speech characteristics, cognitive decline and psychosocial outcomes were subsequently analysed using multiple regression analyses.

Lastly, to evaluate hypothesis 4, linear-mixed modelling and multivariate regression analyses were employed to examine the individual and overall effects of NPIs on cognitive functioning and psychosocial outcomes. P-values of <0.05 were considered statistically significant. Bonferroni corrections were conducted when applicable to reduce false positive rates.

Given that the LFC study has only recently completed data collection, data analyses are still ongoing and specific results are unavailable at the moment. Additionally, given that this is a protocol paper, the authors will focus more on the protocol rather than the results and findings.

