### Visit 1B

The second visit, visit 1B, consisted of psychosocial questionnaires and could be completed either at home or at HAAC. Participants were encouraged to complete visit 1B on paper or online (i.e., using Qualtrics) at home. Those who opted to complete the questionnaires on paper were given the questionnaires during visit 1A. Participants were also given the option to mail their completed questionnaires to a given address, or physically pass the questionnaires back to the research team. If participants were unable to complete the questionnaires at home, visit 1B could be conducted face-to-face at HAAC. Both visits 1A and 1B could be conducted in English or Mandarin, depending on the participant's preference and comfortability with language.

### Visit 2

The last visit, visit 2, was an MRI scan conducted at NUS Clinical Imaging Research Centre (CIRC). Due to budget constraints, this visit was made available to only 300 selected participants. Prior to the scan, participants were briefed on the scan procedures, as well as its potential risks and discomforts. The scan lasted for approximately 30 min. Once the scan concluded, participants were able to request for a copy of the MRI scan images before leaving the centre.

Participants were reimbursed after each visit. Reimbursement for visits 1A, 1B and 2 was $5, $5 and $10, respectively. Fig. 1 below summarizes the flow of the different visits, as well as the different instruments administered during each visit. The instruments utilized in this study were developed through the multi-disciplinary liaison of co-investigators, which allowed for the collection of multi-disciplinary measures.

Fig. 1 shows the flow and instruments administered during each study visit. The visit flow is divided into 5 parts: an introductory phone call, informed consent-taking process, visit 1A, 1B and 2. Participants were introduced and invited to HAAC during an introductory phone call. For the informed consent-taking process at HAAC, their cognitive capacity was screened via MMSE as per NUS-IRB requirements before the study was explained to them and their written informed consent were taken. Visits 1A, 1B and 2 were completed subsequently, consisting of neuropsychological assessments, psychosocial questionnaires and an MRI scan respectively.

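### The cortical-thickness analysis claims family-wise error control but sets the cluster-defining threshold at p<0.05, where the random-field correction does not deliver it

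*Protocol article*

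**What the plan says.** Under Data analysis, for hypothesis 3, "whole-brain vertex-wise associations with behaviour will be analysed using the" standard linear regression module of a named Python library. The correction is then described: "The random field theory (RFT) correction, which corrects the probability of ever reporting a false positive result, was applied with a cluster-defining threshold of" p<0.05. The sentence therefore gives both the aim (controlling the chance of any false positive over the map) and the setting meant to achieve it.

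Three other statements bear on the point:

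- The general significance rule in the same section: "P-values of <0.05 were considered statistically significant".
- The multiplicity rule beside it: "Bonferroni corrections were conducted when applicable to reduce false positive rates".
- The thickness maps, under Image preprocessing, are to be "resampled onto the fsaverage6 space and smoothed using a 5 mm kernel".

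The MRI sample is limited: under Visit 2, "this visit was made available to only 300 selected participants". The article gives no stricter cluster-forming threshold, permutation inference or sensitivity analysis for the thickness maps, and it does not state whether the threshold is one- or two-tailed.

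**The concern.** Cluster inference uses two levels. The cluster-defining threshold decides which vertices join a cluster. A cluster-level p-value then asks whether a cluster that large would be unusual under the null. The random-field formula for the second step assumes a particular distribution of cluster size, and that distribution is derived for high thresholds. At p<0.05 per vertex, neighbouring supra-threshold regions run together and large null clusters are more common than the formula allows. The corrected p-values are then too small.

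If so, the stated aim is not met, and the excess risk recurs for each behavioural variable related to thickness. A Bonferroni adjustment across variables does not help, because it takes the miscalibrated cluster p-values as its input. There is also a problem of interpretation: clusters formed at this level are large, so a significant one says little about where in the cortex the association lies.

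**Working it through.** The threshold is a chosen setting, so the plan has no calculated figure to reproduce. The check is whether the formula holds 5% on null maps.

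**Inputs from the article.** Cluster-defining threshold p<0.05, tail not stated (u = 1.645 one-tailed, 1.96 two-tailed). Significance level 0.05. At most 300 scans, so the test-statistic map is close to Gaussian. 5 mm smoothing kernel.

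**Assumptions, not in the article.** About 100,000 mm² of cortex per hemisphere, modelled as a flat 198 × 198 lattice at 1.6 mm spacing. Effective smoothness of 5 to 20 mm FWHM with Gaussian autocorrelation, plus two long-tailed mixtures (80% at 6 mm with 20% at 25 mm; 70% at 8 mm with 30% at 30 mm).

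**Formula.** For threshold u and cluster size k in lattice points:

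- Roughness: L = 4 ln 2 / FWHM²
- Expected clusters: E[m] = S·L·(2π)^(-1.5)·u·exp(-u²/2), plus small boundary terms
- Expected supra-threshold points: E[N] = 198²·(1 - Φ(u))
- β = (area term of E[m]) / E[N]
- Corrected p = 1 - exp(-E[m]·exp(-βk))

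**Worked case: estimated FWHM 8.09 mm, one hemisphere, one tail.** In lattice units FWHM = 8.09/1.6 = 5.06, so L = 0.1084, with S = 197² = 38,809.

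| Threshold | u | E[m] | E[N] | β | Critical k (points) | mm² | Family-wise error, 1,500 null maps |
|---|---|---|---|---|---|---|---|
| p<0.05 | 1.645 | 118.9 | 1,960.2 | 0.058 | 133.8 | 343 | 13.1% |
| p<0.01 | 2.326 | 42.9 | 392.0 | 0.106 | 63.6 | 163 | 4.9% |
| p<0.001 | 3.090 | 7.1 | 39.2 | 0.178 | 27.8 | 71 | 3.5% |

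The critical k sets the expected number of clusters that large to -ln(0.95) = 0.051. At p<0.05 the observed 13.1% corresponds to -ln(1 - 0.131) = 0.140, about 2.7 times as many. The mean number of clusters was 120.0 against 118.9 predicted, so the count is right and the tail of the size distribution is what fails.

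**Across settings (nominal 5%).** The first column forms clusters at p<0.05 within a tail; the second splits it as 0.025 per tail.

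| Setting | p<0.05 in a tail | Two-tailed p<0.05 | p<0.001 |
|---|---|---|---|
| One hemisphere, one tail: 5, 8, 12, 20 mm | 11.5, 13.1, 10.3, 7.7% | not run | 2.3, 3.5, 3.9, 4.6% |
| Two hemispheres, one tail: 5, 8, 12 mm | 13.0, 13.8, 12.1% | not applicable | not run |
| Two hemispheres, both tails: 5, 8, 12 mm | 15.5, 17.1, 13.6% | 9.1, 10.6, 7.6% | 2.5, 3.5, 3.3% |
| Long-tailed, one hemisphere, one tail | 56%, 53% | not run | 6.6%, 6.5% |
| Long-tailed (first mixture), two hemispheres | 73% one tail, 86% both tails | 62% | 9.5% (both tails) |

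The Monte Carlo standard error is at most about 1.3 percentage points, and every p<0.05 entry is above 5%.

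Periodic fields of known smoothness (grids of 128² to 256², FWHM 8 or 12, which is 256 to 1,024 resels), run more than once, gave 10% to 17% at u = 1.645, 7% to 11% at u = 1.96 and 3% to 5% at u = 3.09.

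**Cluster size.** The median largest null cluster was about 9 to 11 times bigger at one-sided p<0.05 than at p<0.001 in one set of periodic-field runs, and 8 to 19 times in another.

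**The case against.** **Scope.** The specific imaging hypothesis, 3(ii), names functional and structural connectomes, and those are tested with network-based statistics. Thickness enters only through the general wording of hypothesis 3. This stands: one modality, in at most 300 people, is affected.

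**The label may be a slip.** The authors may have meant a corrected cluster-level p<0.05, which matches their general significance rule. On that reading no inflation is shown. The literal reading is the more natural one, however. If the label is wrong, the real cluster-forming threshold is not stated, so the sentence needs correcting either way.

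**The size depends on things the article does not give.** The two-tailed reading brings the rate down to about 7% to 11%, and 20 mm smoothness gives 7.7% even one-tailed. The simulations use flat, stationary fields and the textbook formula, not the named software. This stands against any single figure. It does not change the direction.

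**p<0.001 is partly convention.** Under Gaussian autocorrelation, p<0.01 already gives 3.7% to 5.1%. Under long-tailed autocorrelation, p<0.01 gives about 20% and even p<0.001 gives 6.5% to 9.5%. This is fair, and it favours permutation inference if long-range correlation is suspected.

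**Conclusion.** Wrong as written. The sentence promises control of the family-wise error and sets a threshold at which the correction does not provide it. With stationary Gaussian maps and Gaussian autocorrelation, which suit the method, the true rate is about 1.5 to 3.4 times the nominal 5% (7.6% to 17.1% on the lattice model), depending on tail, smoothness and number of hemispheres. With long-range spatial correlation it could exceed half of all null maps. These figures rest on the assumed surface area, smoothness and textbook formula. The conclusion that the rate exceeds 5% held in every setting tried, on either reading of the tail. It applies to the cortical-thickness results only.

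**What to change.** Set the cluster-defining threshold at p<0.001, with a separate cluster-level family-wise level of 0.05. Alternatively, keep a lower threshold only with permutation-based cluster or threshold-free inference, which does not depend on the high-threshold approximation. Name both levels and the tails in the text, and report thickness findings at the corrected level only. If p<0.05 was meant as the cluster-level criterion, say so and state the cluster-forming threshold actually used.

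The first option is one parameter and a re-run; permutation needs more computing time. In either case weak, diffuse thickness effects are less likely to be declared. The article says that analyses are in progress and nothing has been published, so the change can still be made before results are reported.
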